# Impact of neck percutaneous interferential current sensory stimulation on swallowing function in patients with Parkinson's disease: A single-arm, open-label study protocol

**DOI:** 10.1016/j.conctc.2023.101158

**Published:** 2023-06-10

**Keywords:** Parkinson's disease, Deglutition disorders, Cough, Hypesthesia, Aspiration, Interferential current sensory stimulation

## Abstract

**Background:**

Parkinson's disease (PD) can lead to swallowing dysfunction, resulting in aspiration pneumonia. Among the types of swallowing disorders, a characteristic and serious problem associated with PD is silent aspiration due to pharyngeal and laryngeal hypoesthesia.

**Methods:**

This single-arm, open-label study aims to evaluate the effectiveness of percutaneous neck interferential current sensory stimulation in enhancing swallowing function in patients with PD. The efficacy and safety of percutaneous neck interferential current sensory stimulation will be investigated for patients diagnosed with PD, based on the Movement Disorder Society criteria, of Hoehn–Yahr stages 2–4. The patients will receive neck percutaneous interferential current sensory stimulation for 20 min twice a week for 8 weeks using a Gentle Stim® (FoodCare Co., Ltd., Kanagawa, Japan) device. Once the intervention is initiated, evaluations will be performed every 4 weeks for a 16-week period. The primary endpoint to be assessed is the proportion of patients with normal cough with 1% citric acid at the end of the intervention (8 weeks after intervention initiation) compared with that at the beginning. This clinical trial will examine the usefulness of percutaneous neck interferential current sensory stimulation in patients with PD. In addition, this study will use novel instruments, such as multichannel surface electromyography and electronic stethoscope, to evaluate swallowing function.

**Discussion:**

This novel evaluation can provide insights into dysphagia in patients with PD and the usefulness of percutaneous neck interferential current stimulation. This exploratory study is limited by its single-arm, open-label design and small size.

**Trial registration number:**

jRCTs062220013; pre-results.

## Introduction

1

Neurological diseases can cause swallowing dysfunction that can lead to aspiration pneumonia, resulting in increased patient mortality and morbidity and healthcare costs. Parkinson's disease (PD) is a major neurodegenerative disease with a rapidly rising incidence among aging societies globally, a phenomenon that is called the “Parkinson pandemic” [1]. Aspiration pneumonia is the most common cause of death in patients with PD. Therefore, it is essential to better evaluate and rehabilitate patients with aspiration pneumonia. PD leads to the following types of swallowing disorders: abnormal transport from the oral cavity and pharynx [2], delayed swallowing reflex [3], pharynx residue [4], and others. Among these, hypoesthesia of the pharynx and larynx is particularly serious and is characteristic of PD [4]. The cough test is a simple and useful method for assessing silent aspiration risk [5]. Strengthening swallowing-associated muscles, such as the tongue, soft palate, and suprahyoid muscles, is a useful and established method for swallowing rehabilitation. However, no effective method for preventing silent aspiration and improving sensory function has been established yet.

Recently, several instruments have been developed to stimulate and modulate neurological functions. Percutaneous electrical stimulation of the neck has been found to improve neuromuscular function. To evoke muscle contractions, several types of stimulation methods involving pulsed current stimulation have been found to be effective against various types of dysphagia [6,7] and are widely applied in clinical practice [8]. A drawback of the method is that muscle contraction is painful and invasive. Interferential current sensory stimulation may also be used for treating dysphagia because activation of peripheral sensory nerves in the pharynx and larynx can enhance sensitivity and protect the airway from aspiration [9]. Reports have shown that electrical stimulation devices may improve swallowing function without muscle contraction [10,11]. In addition to motor nerve stimulation for promoting muscle contraction, the stimulation of sensory nerves may be key for improving dysphagia.

Interferential currents can extend to deeper tissues and are more comfortable for the patient than pulsed currents [12]. Thus, they are expected to stimulate sensory nerves in deep layers of the pharynx and larynx without causing discomfort. For these reasons, interferential current stimulation has the potential for reducing dysphagia [13]. Interferential current stimulation reportedly enhances saliva production [14], shortens pharyngeal latency, increases swallowing frequency in healthy men, and increases airway sensitivity [13]. Moreover, for patients with dysphagia, neck percutaneous interferential current sensory stimulation may improve airway defense and nutrition [15].

However, the mechanism underlying swallowing dysfunction improvement in patients with neurological diseases remains unknown, as are the specific effects of device use. Therefore, we aimed to identify the effects of percutaneous interferential current sensory stimulation of the neck on swallowing function of patients with PD via comprehensive swallowing evaluation through videofluoroscopic examination. Sensory functions of the pharynx and larynx will be assessed via a cough test. Moreover, novel instruments, such as multichannel surface electromyography and electronic stethoscope, will be used to evaluate swallowing function in patients with PD.

## Material and methods

2

### Ethics approval

2.1

This study was approved by the Hiroshima University Certified Review Board (approval number: CRB6180006). It has been registered with jRCT (jRCTs062220013). Written informed consent will be obtained from all patients or their relatives.

### Study design

2.2

The first draft of the study protocol, of a single-arm, open-label study, was finalized on February 28, 2022, and the draft adhered to the SPIRIT reporting guidelines [16]. The second amended draft was finalized on December 31, 2022. We designed the study to determine the efficacy and safety of percutaneous neck interferential current sensory stimulation for patients with PD, diagnosed according to the Movement Disorder Society criteria, of Hoehn–Yahr stages 2–4 at Hiroshima University Hospital [17]. This study aims to identify the factors associated with swallowing dysfunction and determine the safety of neck percutaneous interferential current sensory stimulation. Therefore, neither randomization nor blinding was used in this study design. The patient inclusion and exclusion criteria are presented in Table 1.

**Table 1 tbl1:** Eligibility criteria.

Inclusion criteria
1. Diagnosis of clinically probable or established PD based on the Movement Disorder Society criteria 2. PD of Hoehn–Yahr stages 2–4 at the time of registration 3. Levodopa dosage remaining unchanged for more than 1 month 4. Age >19 and < 86 years 5. Able to visit the hospital twice a week 6. Able to provide written informed consent

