**Fig. 2 fig2:**
[figure not shown]
Schema of study timeline.

Evaluations will be performed every 4 weeks from the beginning of the intervention to 16 weeks post-intervention initiation. Videofluoroscopic examinations will be performed every 8 weeks from the beginning of the intervention to 16 weeks post-intervention initiation. The primary, secondary, and exploratory endpoints are listed in Table 2.

**Table 2 tbl2:** Primary, secondary, and exploratory endpoints.

Primary endpoint
The proportion of patients with normal cough reflex after the 1% citric acid cough challenge at the end of the intervention (8 weeks from the initiation). In this study, a normal cough reflex is defined as coughing five or more times 1 min after the consumption of 1% citric acid.

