**Secondary endpoints**
1. Proportion of patients with a normal cough reflex after challenge with 1% citric acid 8 weeks after the last intervention (16 weeks from the initiation of intervention) 2. Proportion of patients with a cough reflex after challenge with 1% citric acid within the first 30 s after the last intervention (8 weeks from the initiation of intervention) 3. Proportion of patients with a cough reflex after 1% citric acid challenge within the first 30 s at 8 weeks after the end of the last intervention (16 weeks from the initiation of intervention) 4. Proportion of patients with normal swallowing status 8 weeks after the end of the intervention (16 weeks after intervention initiation) (normal swallowing status is defined as a Functional Oral Intake Scale score of 7 and an Eating Assessment Tool score of <3) 5. Proportion of patients with a normal swallowing status 8 weeks after the end of the intervention (16 weeks after intervention initiation) 6. Proportion of aspiration and penetration via videofluoroscopic examination at the end point of the intervention (8 weeks after intervention initiation) 7. Proportion of those with aspiration and penetration revealed via videofluoroscopic examination 8 weeks after the end of the intervention (16 weeks after the initiation of the intervention) 8. Incidence of pneumonia onset during the 16-week period after the initiation of the intervention

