### Sample size

2.3

We calculated the required sample size according to preliminary cough tests among patients with neurodegenerative disorders. The proportion of patients with a normal cough reflex after the 1% citric acid challenge required was 28.6%. Assuming that the proportion of patients with a normal cough reflex after 8 weeks of therapy will be 50%, a sample size of 27 participants was estimated, based on an alpha level of 0.10, power of 0.80, and 10% dropout rate.

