### Data acquisition

2.4

Clinical evaluation and diagnosis will be confirmed by two neurologists (MN and HY). The following data will be recorded: body height, weight, body mass index, grip power, calf circumference, disease duration, past medical history, habits of alcohol drinking and smoking, blood pressure, heart rate, oxygen saturation, Unified Parkinson's Disease Rating Scale score [18], medication, Functional Oral Intake Scale score, Eating Assessment Tool-10 score, and blood test values [19]. Cough test, tongue pressure, and peak expiratory flow will be investigated as previously reported [5,20]. Moreover, novel methods, including multichannel surface electromyography, electronic stethoscope, and artificial intelligence system, will be applied. The data will be stored in the Redcap, Electronic Data Capture system. Author YH, who will be blinded to the acquired data, will independently monitor and audit the stored data every week.

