### Data analysis and statistical methods

2.5

Safety analysis will include an evaluation of the proportion of patients with skin symptoms and of exacerbation of neurological symptoms in the head and neck due to the electrical stimulation. If these symptoms are found, the therapy will be discontinued. To assess primary and secondary endpoints, the swallowing status of each patient at the time of the initial intervention will be compared with that at the end of the intervention (8 weeks from the initiation of the intervention) or at 8 weeks after the end of the intervention (16 weeks from intervention initiation). Statistical analysis will be performed using JMP statistical software version 16 (SAS Institute Inc., Cary, NC, USA). As appropriate, the statistical significance of intergroup differences will be assessed using χ^2^ test, Mann–Whitney *U* test, or unpaired *t*-test. We will consider p < 0.05 reflective of statistical significance.

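### Blinding is ruled out as a whole, although videofluoroscopy readers could be masked to visit at little cost in this uncontrolled before/after study

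*Protocol article*

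**What the plan says.** The abstract gives efficacy as the purpose: "This single-arm, open-label study aims to evaluate the effectiveness of percutaneous neck interferential current sensory stimulation". Section 2.2 (Study design) then names the aims of identifying factors associated with swallowing dysfunction and determining safety, and concludes: "Therefore, neither randomization nor blinding was used in this study design". It makes no exception for the people who score outcomes.

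The one role described as blinded is in section 2.4 (Data acquisition): a person "who will be blinded to the acquired data, will independently monitor and audit the stored data every week". That is a monitoring role and is not described as scoring any endpoint.

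The endpoints concerned are in Table 2:

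- **Primary:** "a normal cough reflex is defined as coughing five or more times 1 min after the consumption of 1% citric acid".
- **Secondary 6:** "Proportion of aspiration and penetration via videofluoroscopic examination at the end point of the intervention", with secondary 7 repeating it at week 16.
- **Exploratory 1:** change in bolus passage on temporal videofluoroscopy.

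Section 2.2 schedules videofluoroscopy every 8 weeks up to week 16, that is, at weeks 0, 8 and 16. For the primary and secondary endpoints, section 2.5 sets the comparison within patients: "the swallowing status of each patient at the time of the initial intervention will be compared with that at the end of the intervention", or with that at week 16.

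**The concern.** The word that introduces the decision presents it as following from the aims. It does not follow. Neither a search for associated factors nor a safety assessment prevents a reader from scoring an examination without knowing the visit it came from. The single arm makes it impossible to mask treatment, but masking to time point is a separate matter and remains open.

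This matters more here than in a controlled trial. With two arms, a reader's general tendency to score later visits more favourably would affect both arms and largely cancel. In a before/after comparison without controls, it adds to the estimated change, and no later analysis can separate it out. Aspiration, penetration and bolus timing on videofluoroscopy are reader judgements and so the most exposed. A cough count leaves less room, but a count close to five may still turn on whether a sound is one cough or two.

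**Working it through.** **1. Is outcome reading masked anywhere?** Setting the sections side by side: section 2.2 excludes blinding without qualification; section 2.4 blinds a data monitor; Table 2 and section 2.5 name no masked, independent or central reader and no random reading order. The limitation stated in the abstract and in section 3 concerns the single-arm, open-label design and the small size; it does not mention outcome reading. So no masking of readers is provided, and the text as written excludes it.

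**2. The plan's own figures (section 2.3).** The reference proportion is "The proportion of patients with a normal cough reflex after the 1% citric acid challenge required was 28.6" per cent. The planning assumption is that "the proportion of patients with a normal cough reflex after 8 weeks of therapy will be 50" per cent. Alpha is 0.10 (sidedness not stated), power 0.80, dropout 10%, N = 27.

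The sample size reproduces with a one-sample arcsine formula and one-sided alpha of 0.10:

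- n = [(z₀.₉₀ + z₀.₈₀) / (2·arcsin√0.50 − 2·arcsin√0.286)]² = 23.05, rounded up to 24
- 24 / 0.9 = 26.7, rounded up to 27

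The figure of about 24 evaluable patients is therefore consistent with the plan (27 × 0.9 = 24.3), although the article does not state it. The planned effect is 50 − 28.6 = 21.4 percentage points.

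**3. Weight of one reading (assumption only).** The documents give no misreading rate, so the number of patients moved across the cut is varied from none upwards:

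| Patients reclassified favourably | Shift, n = 24 | Share of 21.4 points |
|---|---|---|
| 0 | 0 | 0% |
| 1 | 1/24 = 4.2 points | 19% |
| 2 | 2/24 = 8.3 points | 39% |

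If all 27 patients are evaluable, two reclassified patients give 2/27 = 7.4 points, or 35%. The 21.4 points belong to the primary endpoint; the article states no planned effect for videofluoroscopy, so for those endpoints only the 4.2 points per patient carries over.

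**4. Effect on a false-positive rate (also assumption only).** Take a one-sided exact binomial test of 28.6% with n = 24 and alpha 0.10. It needs 11 or more normal results. Suppose there is no true effect and a fraction b of truly abnormal week-8 tests is scored normal, so that the apparent proportion is 0.286 + b × 0.714:

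- b = 0: 5.4%
- b = 5%: 11.4%
- b = 10%: 20.5%
- b = 20%: 46.2%

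Neither this test nor any value of b is stated in the article. The list shows sensitivity to misreading and is not an estimate of bias.

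**The case against.** The strongest case on the other side has four parts.

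- **The sentence may refer only to treatment.** It pairs blinding with randomization in an open-label study, and an article may leave reading procedures to the full protocol. In part this stands: a reader might infer that assessors will certainly know the visit, or that videos are stored and read later, but the article says neither. It does not say who counts coughs, who reads videofluoroscopy or what they know. What remains is that the article makes a positive, unqualified statement and gives a reason that does not support it.

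- **The size is not known.** This stands. A reader might take 39% as the bias to expect. It is only what two reclassified patients would amount to; with none it is zero.

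- **The primary endpoint is a count of discrete events.** This largely stands. A reader might infer that the primary result is as exposed as videofluoroscopy and that its count should be moved to masked recordings. The documents do not support either step. Section 2.6 has the study running from June 2022, and the article appeared in June 2023, so some baseline tests may exist only as live counts. A change made now could set a live, unmasked baseline against a masked, recorded week 8 in the same patient, which would bring in a new bias.

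- **The limitation is disclosed and the study is exploratory.** The design limitation is admitted, and this lowers the severity. It does not answer the point, because reader masking is possible within that design.

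**Conclusion.** The point holds in a limited form. The plan excludes all blinding on grounds that justify only unmasked treatment, and the uncontrolled within-patient comparison leaves reader expectation free to add to the apparent effect. This applies most clearly to secondary endpoints 6 and 7 and exploratory endpoint 1, and possibly to cough counts near five. The direction and amount of any bias cannot be derived from the documents. The only firm size is the leverage of one patient: 4.2 points if about 24 are evaluable.

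The sample size is not in question here and need not change. Severity is low: this is an inexpensive improvement to an openly exploratory study. Masked reading would deal with reader bias only; patient expectation and regression to the mean would remain.

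**What to change.** In section 2.2, replace the blanket statement with wording such as: *Treatment is not blinded. Videofluoroscopy recordings from weeks 0, 8 and 16 are coded, stripped of visit labels, shuffled across patients and visits, and scored for the research endpoints by existing readers masked to time point, where possible not the person who made the same-day clinical reading.* Shuffling across patients as well as visits makes the order harder to guess than reading one patient's three examinations together.

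Keep the live cough count as the primary measurement. Where the test was recorded at both baseline and week 8 for the same patient, add a masked recount as a sensitivity analysis. Do not mix live and recorded counts within a patient.

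The cost is file handling and later research scores. Same-day clinical reading is unaffected. The change depends on recordings being kept, which the article does not state. If cough tests are not already recorded, recording them would be an added procedure and may need an amendment and consent wording, so that part should stay optional.

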**Exclusion criteria**
1. Pacemaker or implantable defibrillator 2. Ongoing treatment with deep brain stimulation 3. Currently pregnant or trying to become pregnant 4. Currently diagnosed with or having a history of head or neck cancer 5. Active pneumonia 6. History of swallowing rehabilitation 7. Exclusion considered appropriate by doctors

Fig. 1 shows the SPIRIT schedule of enrollment, interventions, and assessments. Schematics outlining the study timeline are presented in Fig. 2. The patients will undergo neck interferential current sensory stimulation for 20 min twice a week for 8 weeks. A Gentle Stim® (FoodCare Co., Ltd., Kanagawa, Japan) device will be used for stimulation. Pads will be attached to the front of the neck to stimulate the swallowing-related (superior laryngeal) nerve. The swallowing reflex interferential current (50 Hz) stimulation threshold is lower than the pulse stimulation; therefore, patients may scarcely feel the stimulation. The patients will be stimulated according to a unified protocol involving maximum stimulation current below the threshold at which the patient perceives electrical stimulation, ranging from 2.0 mA to 2.5 mA. Stimulation will be performed regularly and repetitively.

**Fig. 1 fig1:**
[figure not shown]
SPIRITschedule of enrollment, interventions, and assessments.

**Fig. 2 fig2:**
[figure not shown]
Schema of study timeline.

Evaluations will be performed every 4 weeks from the beginning of the intervention to 16 weeks post-intervention initiation. Videofluoroscopic examinations will be performed every 8 weeks from the beginning of the intervention to 16 weeks post-intervention initiation. The primary, secondary, and exploratory endpoints are listed in Table 2.

**Table 2 tbl2:** Primary, secondary, and exploratory endpoints.

Primary endpoint
The proportion of patients with normal cough reflex after the 1% citric acid cough challenge at the end of the intervention (8 weeks from the initiation). In this study, a normal cough reflex is defined as coughing five or more times 1 min after the consumption of 1% citric acid.

**Secondary endpoints**
1. Proportion of patients with a normal cough reflex after challenge with 1% citric acid 8 weeks after the last intervention (16 weeks from the initiation of intervention) 2. Proportion of patients with a cough reflex after challenge with 1% citric acid within the first 30 s after the last intervention (8 weeks from the initiation of intervention) 3. Proportion of patients with a cough reflex after 1% citric acid challenge within the first 30 s at 8 weeks after the end of the last intervention (16 weeks from the initiation of intervention) 4. Proportion of patients with normal swallowing status 8 weeks after the end of the intervention (16 weeks after intervention initiation) (normal swallowing status is defined as a Functional Oral Intake Scale score of 7 and an Eating Assessment Tool score of <3) 5. Proportion of patients with a normal swallowing status 8 weeks after the end of the intervention (16 weeks after intervention initiation) 6. Proportion of aspiration and penetration via videofluoroscopic examination at the end point of the intervention (8 weeks after intervention initiation) 7. Proportion of those with aspiration and penetration revealed via videofluoroscopic examination 8 weeks after the end of the intervention (16 weeks after the initiation of the intervention) 8. Incidence of pneumonia onset during the 16-week period after the initiation of the intervention

